### Consent and withdrawal from study

Child welfare caseworkers obtain written informed consent and release of information from all parents at intake prior to study enrollment. Kinship caregivers consent for their own participation. Participation is voluntary and participants are free to withdraw from the study at any time without consequences to their child welfare cases.

### Collaboration, coordination and cross-training

Child welfare-involved parents with substance use disorders must navigate multiple systems including behavioral health, and juvenile/family courts in order to complete case plans. To facilitate collaboration and coordination of services for EPIC, all partner agencies entered into one comprehensive memorandum of understanding (MOU) to jointly administer and implement EPIC. All partner agencies further agreed to use the Needs Portal [34], a hybrid web-based resource and referral and Management Information System (MIS), as the organizing body for communication around each case. The Needs Portal is used to create referrals for services, track dates of service provision, and record responses to the UNCOPE and trauma screening and assessment tools. The system works by opening a ‘ticket’ for each case which allows caseworkers to complete substance abuse and trauma assessments and indicate essential information about service requests. Service providers respond to requests and indicate when services have been initiated and peer recovery supporters are able to log visits with participants, all within the same environment. Caseworkers, service providers, and the evaluation team can see this information. Lastly, the Needs Portal provides differential access to the system based on the role of the provider to limit access of information based on a person’s assigned role in the case (i.e., caseworker, therapist, peer recovery supporter).

Prior to implementation, partner agencies also received cross-system training such that child welfare workers become more knowledgeable of substance misuse and trauma-informed care, peer recovery supporters understand the child welfare system and processes, and family drug court coordinators and MOUD providers have a thorough understanding of the child welfare system. Representatives from each system are also members of a Steering Committee that meets every other week, to resolve any implementation related problems and address barriers.

### Evaluation design

To evaluate EPIC, a quasi-experimental design will be employed through a two-stage sampling procedure. This design provides the ability to assess (1) the effects of EPIC on access to services for the families in the two intervention counties, and (2) the independent effects of additional services provided under EPIC that may be over and above interventions provided by Ohio START and treatment as usual (TAU). In the first stage, two comparison counties will be identified for each of the two intervention counties. One comparison county will be part of the Ohio START program while the second will be a county that has no major interventions to address substance use among child welfare families. Counties are matched based on child population size, rate of child protective services referrals, percent of naloxone administrations per adult population, percent white, percent poverty, child welfare tax levy, and to the extent possible, behavioral health service availability. During the second stage, EPIC families (*N* = 250) are matched with substance using families in Ohio START (*N =* 250) and those receiving treatment as usual (*N =* 250).

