### Rationale for study

Both counties have taken significant steps to address the needs of families, including the implementation of Ohio START (Sobriety, Treatment, and Reducing Trauma) [17].

Fairfield and Pickaway counties also have Family Treatment Drug Courts (FTDC) in operation. FTDC includes frequent court hearings, judicial monitoring, substance abuse treatment, drug testing, and rewards and sanctions linked to parental compliance with service plans [18]. However, only six residential or intensive outpatient substance use providers are located within the boundaries of the two counties, with only one providing residential or detoxification facilities. While a 31bed facility recently opened in Pickaway county [19], the demand for detoxification beds still outweighs the current supply. Fairfield County has little infrastructure to support the use of medications for opioid use disorders (MOUD) and has not used it systematically for child welfare families. Further, while service providers and local governments tend to think in terms of county lines, families do not use that same thought process when seeking help. In this way, the patchwork structure of alcohol and other drug (AOD) services inhibits the ability of both counties to address the AOD needs of families involved in the child welfare system.

Funded by the federal Regional Partnership Grant (RPG) Program, the Enhancing Permanency in Children and Families (EPIC) is a partnership between child welfare, juvenile count court  and behavioral health, to holistically address substance misuse and associated parenting needs of child welfare-involved families.

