### Study components

EPIC participants are incentivized to participate in (1) family treatment drug court (FTDC), with medications for opioid use disorders (MOUD); (2) peer recovery support and (3) home-based parenting supports based on the Nurturing Parenting Program [20].

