#### FTDC with MOUD

FTDC is considered the most effective intervention to improve substance abuse treatment initiation and completion in child welfare populations [21]. Parents who participate in FTDC are more likely to enter substance use treatment, get into treatment quicker, stay in treatment longer, and complete treatment more often [22–24]. Additionally, families who complete FTDC are more likely to be reunified with their children as compared to parents who do not participate [22–25]. To bolster the effects of FTDC, EPIC participants also have access to MOUD, which has been shown to reduce withdrawal symptoms, lower the risk of relapse, address cravings, and provide medical supervision for individuals struggling with addiction [26]. Further, MOUD is associated with an increased likelihood that children will remain in their parents’ custody [27].

*Peer recovery supporters*—also called “recovery coaches”— are advocates for parents and their primary focus is to help get parents into treatment and support them so that they stay there. Peer recovery supporters are certified by the Ohio Department of Mental Health and Addiction Services [28] and must complete 40 h of in-person training, 16 h of online training, and pass a test. They are individuals who formerly had substance use issues, but have been clean and sober for at least 3 years. Peer recovery supporters provide comprehensive clinical assessments, service planning, referral, advocacy, case management, and outreach services. Peer recovery supporters have had great success in reducing substance use and improving child welfare outcomes. Peer recovery supporters improve access to substance use treatment, decrease time children spend in out-of-home care, increase the odds of reunification, decrease maltreatment recidivism, and reduce racial disparities in reunification [29–31]. Under EPIC, peer recovery supporters are trained and supervised by two partner behavioral health agencies, Ohio Guidestone and Integrated Services. Peer recovery supporters make individual or joint home visits with child welfare caseworkers and are otherwise available via phone and text as needed. They also attend multi-disciplinary child welfare team meetings to provide expert consultation on cases.

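### Drug courts already operating in the EPIC counties are not matched on, so the cross-county comparison cannot isolate the effect of the services EPIC adds

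*Protocol article*

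**What the plan says.** **Existing services.** Rationale for study, setting out the background to EPIC, states "Fairfield and Pickaway counties also have Family Treatment Drug Courts (FTDC) in operation". It also says of the same two counties: "Both counties have taken significant steps to address the needs of families, including the implementation of Ohio START".

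**The intervention.** Study components lists FTDC, with MOUD, first among the three things EPIC participants are paid or encouraged to take up. Peer recovery support and home-based parenting support are the other two.

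**The comparators.** Under Evaluation design, each EPIC county gets two comparison counties: "One comparison county will be part of the Ohio START program while the second will be a county that has no major interventions". The matching list begins "Counties are matched based on child population size, rate of child protective services referrals, percent of naloxone administrations per adult population, percent white", continues with poverty, and ends "child welfare tax levy, and to the extent possible, behavioral health service availability". No item refers to drug courts.

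**The claim.** The same section says the design can assess "the independent effects of additional services provided under EPIC that may be over and above interventions provided by Ohio START and treatment as usual".

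**FTDC and the outcomes.** The FTDC with MOUD section credits these courts with quicker, longer and more complete treatment, and adds that "families who complete FTDC are more likely to be reunified with their children as compared to parents who do not participate". Reunification is one of the outcomes compared.

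**A competing account.** Participant recruitment, eligibility and group assignment says eligible parents are alternated among EPIC, Ohio START and TAU. The Abstract and Evaluation design instead draw the comparison groups from other counties.

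**The concern.** FTDC appears twice in this design: as a standing service of the EPIC counties and as an EPIC component. Some EPIC families would have gone through the drug court anyway. Their outcomes count towards EPIC, while the TAU counties are selected by a rule that, on a plain reading, tends to exclude counties with such a court. For the Ohio START counties, FTDC status is left to chance.

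The difference lies at county level, so matching families within counties does not remove it. With two EPIC and two TAU counties, regression adjustment can hardly do so either. What is at stake is the claim about added services: a favourable EPIC versus TAU result could come wholly or partly from a court that was already there, and the stated analyses could not tell.

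**Working it through.** The plan gives no figure for this, so there is none to reproduce. The check sets the sections side by side and then illustrates the possible size.

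**1. What each contrast contains**

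- EPIC families: EPIC's additions plus FTDC, part of which would have been used without EPIC.
- TAU-county families: usual services in a county chosen for lacking a major substance-use intervention. Whether an FTDC counts as one is not stated. Rationale for study describes it as judicial monitoring with treatment and drug testing, so it plausibly does.
- Ohio START-county families: START, with or without an FTDC. The document does not say which.

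EPIC versus TAU is therefore additions plus background FTDC. EPIC versus START is the same unless the START counties happen to have drug courts.

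**2. Whether the stated analyses remove it**

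The Statistical plan names survival analysis for days in care, logistic regression for reunification and later investigations, linear regressions, and paired t-tests from baseline to 6 months. The paired tests compare families with themselves, and the power calculation gives them N = 250, one group's size. They do not compare counties. For the outcomes taken from SACWIS, the statewide child welfare data system, no pre-EPIC county comparison is stated.

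**3. Illustration with EPIC's additions set to zero**

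From the document: 250 families per group and alpha 0.05. Assumed: a two-sided test, no FTDC in TAU counties, reunification *p0* = 40% without FTDC and *pF* = 60% with it, and background uptake *u* of 10%, 30% or 50%.

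- EPIC rate: *p1* = *p0* + *u*(*pF* − *p0*)
- Standard error: SE = √[*p0*(1 − *p0*)/250 + *p1*(1 − *p1*)/250]
- Chance of significance in EPIC's favour: Φ(*z* − 1.96), with *z* = (*p1* − *p0*)/SE

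| *u* | *p1* | Spurious difference | SE | *z* | Chance |
|---|---|---|---|---|---|
| 10% | 42% | 2 points | 0.044 | 0.45 | about 7% |
| 30% | 46% | 6 points | 0.044 | 1.36 | about 27% |
| 50% | 50% | 10 points | 0.044 | 2.26 | about 62% |

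Without confounding the chance is 2.5%. Clustering by county is ignored.

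**4. Sensitivity to the assumptions**

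Now take *p0* = 50%, an FTDC odds ratio from 1.25 to 2.0 and uptake from 25% to 100%.

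- Low end: *pF* = 1.25/2.25 = 55.6%; 0.25 × 5.6 = 1.4 points; chance about 5%.
- Middle (odds ratio 1.5, half uptake): *pF* = 60%; 0.5 × 10 = 5 points; chance about 20%.
- High end: *pF* = 2/3 = 66.7%; 1.0 × 16.7 = 16.7 points; chance about 97%.

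The range runs from negligible to decisive, and nothing in the document narrows it.

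**The case against.** **FTDC is a declared EPIC component.** Objectives 2.1 to 2.3 compare EPIC families with substance-affected families not receiving EPIC, which is a package contrast. FTDC use that EPIC brings about is then treatment, not contamination. This stands, and it narrows the point to FTDC use that would have occurred anyway and to the claim about additional services.

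**Comparators may come from within the EPIC counties.** If eligible parents are alternated as the recruitment section says, all groups share the same courts and the problem largely goes away. But the Abstract and Evaluation design say otherwise. The contradiction determines how far the confounding exists, so it must be settled.

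**The bias could run the other way.** Rationale for study describes scarce treatment provision in the EPIC counties. Need for services gives substance problems in 79% and 67% of child welfare families, against 50% statewide. Matching on behavioral health availability may also absorb part of the service difference. All this stands: the net direction is unknown.

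**The illustrated effect may be too large.** The document's reunification statement concerns families who complete FTDC, compared with non-participants. Applying a 20-point gain to everyone who enters treats that as a causal effect on all users.

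A reader might also infer that Ohio START is being credited to EPIC, because both counties have implemented it. The document does not support that: the recruitment section makes START an alternative assignment to EPIC, and nothing says EPIC families receive both. Nor is the TAU comparison one against no services, since those families receive usual care.

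**Conclusion.** The point holds for FTDC. As Evaluation design is written, background drug-court use is inseparable from EPIC's additions in the EPIC versus TAU contrast, and possibly in EPIC versus Ohio START, depending on a county characteristic that is neither matched nor reported. The claim to assess the independent effects of added services is not supported.

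This rests on three readings: that the courts described in the rationale were operating before EPIC began, that the comparators come from other counties, and that counties without a major intervention mostly lack an FTDC. The 2 to 10 point differences, and the wider 1.4 to 16.7 points, are illustrations on assumed uptake and effect. They show that the problem could matter. They do not estimate the bias, and part of any observed effect may be genuine.

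**What to change.** 1. **Match on FTDC.** Add presence of an operating FTDC to the matching list for the Ohio START comparison counties. Cost: one variable and a smaller pool of counties. This will not repair EPIC versus TAU, because requiring an FTDC would work against the rule by which TAU counties are chosen.

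2. **Add a supporting difference-in-differences analysis, for SACWIS outcomes only** (days in care, reunification, new referrals). Use all six counties (2 EPIC + 4 comparison) and a pre-EPIC period in which the FTDCs were already operating. The estimate is the pre-to-post change in EPIC counties minus that in comparison counties. Cost: one further extract of data already received quarterly, and a period-by-group term. Downsides to state: lower precision, the need to identify substance-affected families in earlier records, and reliance on parallel trends with only two EPIC counties. That last assumption is strained, because Pickaway's out-of-home count rose from 23 in 2013 to 73 in 2018 while Fairfield's custody numbers were described as steady. FTDC start dates are not given and must be established first.

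3. **Narrow the claim.** Describe EPIC versus TAU, including the survey outcomes, which the pre-EPIC extract cannot reach, as the effect of the whole package plus county service context. Cost: wording only.

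4. **Reconcile the source of comparators.** Make the recruitment section agree with the Abstract and Evaluation design. If there are within-county comparators, say so, since they would share the FTDC background.

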**Methods:**

EPIC is a quasi-experimental study. Under the program**,** child welfare-involved adults who screen positive for substances are matched with a peer recovery supporter. Participants are also incentivized to participate in family treatment drug court, medications for opioid use disorders and home-based parenting supports. Participating adults (*N* = 250) are matched with comparison groups from counties participating in a separate intervention (Ohio START) and to those receiving treatment as usual, resulting in a final sample of 750 adults. Primary outcomes including addiction severity, child trauma symptoms, resilience, and attachment are assessed at baseline and at program completion. Additional outcomes include timely access to treatment services, length of placement in out-of-home care and recidivism into the child welfare system.

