### Participant recruitment, eligibility and group assignment

Participants are recruited from Fairfield and Pickaway County Children Services. The overall case flow is provided in Fig. 1. Within 7 days of the initial child welfare investigation, parents complete the UNCOPE assessment, a universal screening tool for substance use administered to all parents entering the child welfare system [33]. Parents who score a 3 or higher on the UNCOPE, are considered eligible for EPIC and receive a drug screen. Eligible parents are alternated into EPIC, OhioSTART or treatment as usual (TAU). Ultimately, assignment to EPIC is determined based on caseload, but is typically offered to every third case in Fairfield county and every other case in Pickaway county. Parents who consent to EPIC are connected to peer recovery supporters who mentor parents through the process. Parents are also referred to FTDC with the option to receive MOUD, and lastly when children are placed at home with parents or with kinship caregivers, relational skill building services that include financial assistance for child care, respite and transportation services. EPIC participants receive substance abuse and behavioral health treatment services through local providers including from two partner agencies: Integrated Services for Behavioral Health and Ohio Guidestone.

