### Statistical plan

Baseline descriptive statistics including sociodemographic characteristics, addiction severity and child welfare allegations will be provided for EPIC participants and comparison groups. For continues variables, means and SDs will be provided and for categorical variables, counts and percentages are provided.

Due to the likelihood of censored measures when families are still involved in the child welfare system, survival analysis will be utilized to assess program effects on length of stay in out of home care. Logistic regressions will be used to estimate the relationship between activities and family was reunification, subsequent child maltreatment investigations, and subsequent child maltreatment substantiations. A series of linear regressions will be used to estimate the relationship between our outcome measures and various independent variables (e.g., age, biological sex). Additionally, a paired samples t-test will be conducted to examine the changes in mean scores in child, parent and caregiver well-being outcomes (e.g. ASI or CBCL) between baseline and 6-months follow-up.

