#### Power analysis

We performed a series of power analyses using G*Power [44] and for each analytic method. Assuming a small effect size of 0. 2, we will be able to reject the null hypothesis with probability (power) of 1.00 (survival analysis, *N* = 750), 0.81 (logistic regression, *N* = 750), 0.88 (paird t-tests; *N* = 250) and 0.99 (linear regression, *N* = 250). The Type I error probability associated with these tests is 0.05. A detailed report is presented in Additional file 1.

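### Comparison groups drawn from their own counties, two per group, while the N = 750 power and the 0.05 error rate carry no stated allowance for county

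*Protocol article*

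**What the plan says.** The Evaluation design section sets out two-stage sampling. In the first stage, "two comparison counties will be identified for each of the two intervention counties", and of each such pair "One comparison county will be part of the Ohio START program while the second will be a county that has no major interventions". In the second stage 250 EPIC families are matched to 250 Ohio START and 250 treatment-as-usual (TAU) families. The abstract also takes the Ohio START comparators from other counties, "resulting in a final sample of 750 adults".

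The section on participant recruitment, eligibility and group assignment, which concerns families in Fairfield and Pickaway, gives a different account: "Eligible parents are alternated into EPIC, OhioSTART or treatment as usual (TAU"). It continues: "Ultimately, assignment to EPIC is determined based on caseload, but is typically offered to every third case in Fairfield county". For Pickaway the usual rate is one case in two.

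In the Statistical plan, "survival analysis will be utilized to assess program effects on length of stay in out of home care". Logistic regression is named for reunification and for later investigations and substantiations. No county effect, cluster-robust variance or matched-set term is mentioned.

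The Power analysis section reports: "Assuming a small effect size of 0. 2, we will be able to reject the null hypothesis with probability (power) of 1.00" for survival analysis (N = 750), 0.81 for logistic regression (N = 750), 0.88 for paired t-tests (N = 250) and 0.99 for linear regression (N = 250). It adds: "The Type I error probability associated with these tests is 0.05". A detailed report is said to be in Additional file 1, which is not at hand.

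**The concern.** Under the Evaluation design section, group is a property of the county. Families in one county share a children services agency, a juvenile court and a local supply of treatment, so placement length, reunification and re-referral may be correlated within county. Matching families on their own characteristics does not remove what they share through the county.

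A model that treats 750 families as independent measures only the variation between families. Any county-to-county difference left after matching then enters the estimated program effect without entering its standard error. At stake are the child safety and permanency outcomes: an ordinary difference between counties could be reported as an EPIC effect, with an interval that is too narrow and a p-value that is too small.

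**Working it through.** **Inputs.** From the article: two counties per group (Evaluation design); 250 families per group, 750 in all (abstract, Evaluation design); effect size 0.2, alpha 0.05 and the four power values (Power analysis). Assumed: an even split, so m = 250/2 = 125 families per county; a county ICC between 0.001 and 0.05; two-sided tests.

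**The plan's own figures, treating families as independent.**
- Paired t-test, standardised change 0.2, n = 250, two-sided: power 0.883. This reproduces 0.88; one-sided gives 0.934 and does not.
- Linear regression, f² = 0.2, n = 250: 1.000 with 1 to 5 predictors and 0.997 with 20, consistent with 0.99.
- Logistic regression, N = 750: not uniquely reproducible, because event rate, odds ratio and sidedness are not in the article. Settings that come close to 0.81 include an odds ratio of 1.25 per SD with a 30% event rate, two-sided (0.800), and a log odds ratio of 0.2 per SD with a 30% event rate, one-sided (0.807).
- Survival analysis, N = 750: not uniquely reproducible. A log hazard ratio of 0.2 with 750 events gives 1.00 for a covariate per SD, but 0.78 (1:1) or 0.73 (1:2) for a two-group contrast.

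Every setting that comes close uses independent observations with no design effect.

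**Allowing for county.**
- Design effect DE = 1 + (125 − 1) × ICC. At ICC 0.01: 1 + 124 × 0.01 = 2.24.
- Effective N = 750/DE. At ICC 0.01: 750/2.24 = 335.
- True error of a nominal two-sided 5% test = 2 × Φ(−1.96/√DE). At ICC 0.01: 2 × Φ(−1.31) = 0.19.
- Logistic power, rescaled from 0.81 = Φ((1.96 + 0.878)/√DE − 1.96). At ICC 0.01: Φ(1.896 − 1.96) = 0.47.
- Survival power, rescaled in the same way from 0.995, the lowest value that rounds to 1.00. The result is therefore a lower bound.

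| ICC (assumed) | DE | Effective N | True error | Logistic power (stated 0.81) | Survival power, lower bound (stated 1.00) |
|---|---|---|---|---|---|
| 0.001 | 1.12 | 667 | 6.5% | 0.76 | 0.99 |
| 0.005 | 1.62 | 463 | 12% | 0.61 | 0.95 |
| 0.01 | 2.24 | 335 | 19% | 0.47 | 0.86 |
| 0.02 | 3.48 | 216 | 29% | 0.33 | 0.68 |
| 0.05 | 7.20 | 104 | 47% | 0.18 | 0.39 |

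The power columns use a normal reference and so ignore the very small number of counties.

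**Could a county-level test repair this?** EPIC against one comparison group is 2 v 2 counties, which leaves 2 degrees of freedom (critical t 4.30), or 1 if the matched county sets are respected (critical t 12.71). With 2 degrees of freedom and a standardised difference of 0.2, the noncentrality at ICC 0 is 0.2/√(2/250) = 2.24 and the power is 0.26. It is 0.15 at ICC 0.01. A permutation test has 6 arrangements, so its smallest two-sided p-value is 2/6 = 0.33; within the two matched sets there are 4 arrangements and the smallest is 2/4 = 0.50. No conventional county-level test can support the claim.

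**The case against.** **Silence is not absence.** This is a condensed article. A county term or robust variance is often left to the analysis plan, and Additional file 1 is not shown. This stands: one can say only that no allowance is named. But the article does more than stay silent. It states power values and an error rate, and these do not hold for the outside-county contrast if county outcomes vary.

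**Assignment may not be by county.** A reader might infer that treatment is simply assigned by county. The recruitment section does not support that: alternation within Fairfield and Pickaway would not nest group in county. This stands as a reason to reconcile the sections. It does not remove the point, because the Evaluation design section and, for Ohio START, the abstract both describe outside-county comparators.

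**Not every analysis is touched.** A reader might extend the point to all four methods. Only survival and logistic power use N = 750. The paired t-test is a within-group change, and the linear models (N = 250) are described through predictors such as age and sex. Both lie outside this point. The logistic models are described as relating activities to outcomes; N = 750 shows that all three groups enter them, but only the survival analysis is tied in words to program effects.

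**The ICC is assumed.** This stands. The relevant ICC is what remains after counties and families have been matched, and at 0.001 the harm is small. It is also tempting to say that the introduction shows the study counties to differ. It contrasts only the two EPIC counties (for instance 48.09 v 14.29 investigations per 1000 children) and says nothing of the comparison counties. That makes between-county variation plausible but does not size it.

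**Conclusion.** The point holds for the between-group survival and logistic analyses under the Evaluation design section. With two counties per group, the N = 750 power of 1.00 and 0.81 and the 0.05 error rate are stated without any county design effect and do not apply to the outside-county contrast if the county ICC is above zero.

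The size depends on an ICC that the article does not give. Over 0.001 to 0.05, with about 125 families per county, the true error of a nominal 5% test runs from 6.5% to 47%, and logistic power from 0.76 down to 0.18. An uneven split of families between counties would raise the design effect at the same ICC.

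Correcting the standard error would not be enough: two counties per group leave county differences confounded with group. Separately, and without any assumption, the article gives two incompatible accounts of where the comparison families come from.

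**What to change.** 1. Reconcile the recruitment and Evaluation design sections, and state which comparison groups are used for which analysis.
2. For outside-county contrasts, restate the N = 750 power over a range of ICCs, and withdraw the claim that family-level tests hold a 0.05 error.
3. Show results by county and by matched county set. Label family-level intervals as not covering between-county variation, and do not attribute a difference to EPIC on the family-level p-value alone.
4. Where earlier cohorts of substance-affected families can be identified in the state administrative child welfare data (SACWIS), add a difference-in-differences comparison as a supporting analysis. The article does not say whether they can.
5. Stratify any in-county contrast by county, and report as a limitation that assignment depended on caseload. It avoids the nesting problem but is open to selection, so it is not a clean substitute.

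Items 1 to 3 and 5 cost wording and some recalculation; item 4 needs earlier years of administrative data. The downside is wider stated uncertainty, less favourable power and a more guarded conclusion about EPIC against other counties.
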